**Methods and analysis:**

This single-centre, prospective, interventional cohort study will investigate the effectiveness of a biomechanically monitored targeted exercise protocol combined with Traditional Chinese Medicine (TCM) compared with conventional exercise combined with TCM in patients with patellofemoral pain syndrome (PFPS). We will consecutively recruit 96 eligible patients. Participants will be assigned to either an experimental group or a control group based on their preference after receiving standardized information. The experimental group will receive biomechanical monitoring, targeted exercise, and Traditional Chinese Medicine (TCM), whereas the control group will receive conventional exercise and the same TCM regimen.

Outcomes will be assessed at baseline, 6 weeks, 6 months and 3 years post-intervention. The primary outcome measure will be pain intensity measured using the Visual Analog Scale (VAS). Secondary outcome measures will include: biomechanical parameters; pain (Knee Pain Scale); joint function (Lysholm Knee Scoring Scale); kinetic parameters (mean power and pulling acceleration during stair climbing using the IDEEA system); spatiotemporal gait parameters (walking speed, step frequency, double support time during stair climbing using IDEEA); and quality of life (36-Item Short Form Health Survey).

For statistical analysis, independent samples *t*-tests will be used for between-group comparisons, and linear mixed-effects models will be applied for outcomes measured at multiple time points. To control for expectation bias, patients' treatment expectation scores will be recorded at baseline and adjusted as covariates if significant between-group differences exist. Baseline characteristics will be compared, and any imbalanced variables will be included as covariates in the primary analysis. A two-tailed *P*-value < 0.05 will be considered statistically significant.

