### Group allocation and intervention

2.5

Patients will be assigned to either the experimental group or the control group based on their preference after receiving standardized information about both interventions. Specifically, the experimental group will receive biomechanical monitoring, targeted exercise, and Traditional Chinese Medicine (TCM), whereas the control group will receive conventional exercise and the same TCM regimen as the experimental group.

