#### Secondary outcomes

3.1.2

Secondary outcomes include the following: biomechanical parameters, assessed by changes from baseline in patellar tracking using dynamic radiography and three-dimensional gait analysis; pain, measured by the Knee Pain Scale (KPS) (26); joint function, evaluated by the Lysholm Knee Scoring Scale (27, 28); kinetic parameters measured by the IDEEA system during stair climbing, including mean power (W) and pulling acceleration (g); spatiotemporal gait parameters measured by the IDEEA system during stair climbing, including walking speed (m/s), step frequency (steps/min), and double support time (ms); and quality of life, assessed by the 36-Item Short Form Health Survey (SF-36) (29–31).

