#### Statistical analysis

3.2.2

Data will be analyzed using SPSS software (version 26.0, IBM Corp., Armonk, NY, USA). Continuous variables will be presented as mean ± SD, and categorical variables as frequency (n) and percentage (%). The primary outcome is the change in VAS score from baseline to 6 weeks, and an independent samples *t*-test will be used to compare the change scores between the two groups. For outcomes measured at multiple time points (baseline, 6 weeks, 6 months, and 3 years), a linear mixed-effects model will be employed to account for within-subject correlations and to handle missing data under the missing at random assumption, including group, time, and group-by-time interaction as fixed effects and subjects as random effects.

As this is a non-randomized study, baseline characteristics (including age, sex, body mass index, and baseline VAS score) will be compared between groups, and if any significant imbalance is detected, these variables will be included as covariates in the primary analysis to adjust for potential confounding. Secondary outcomes will be analyzed using independent samples *t*-tests for continuous variables and chi-square tests for categorical variables. Missing data will be handled using multiple imputation for sensitivity analysis. A two-tailed *P*-value < 0.05 will be considered statistically significant for all analyses.

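### Secondary outcomes are assigned both to a mixed model and to t-tests, and neither analysis as written adjusts for confounding between groups formed by patient preference

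*Protocol article*

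**What the plan says.** All references are to the protocol article.

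- **Allocation (section 2.5).** "Patients will be assigned to either the experimental group or the control group based on their preference", after standardized information about both interventions.
- **Visits (abstract).** "Outcomes will be assessed at baseline, 6 weeks, 6 months and 3 years post-intervention". Section 3.1.2 lists patellar tracking, the Knee Pain Scale, Lysholm, five IDEEA stair-climbing parameters and SF-36, and exempts none of them from this schedule. Its list opens with "Secondary outcomes include the following: biomechanical parameters, assessed by changes from baseline in patellar tracking".
- **First rule (section 3.2.2, first paragraph).** "For outcomes measured at multiple time points (baseline, 6 weeks, 6 months, and 3 years), a linear mixed-effects model will be employed", with the model "including group, time, and group-by-time interaction as fixed effects and subjects as random effects". The abstract agrees: "linear mixed-effects models will be applied for outcomes measured at multiple time points".
- **Second rule (section 3.2.2, second paragraph).** "Secondary outcomes will be analyzed using independent samples" t-tests if continuous, and chi-square tests if categorical.
- **Covariates.** Section 3.2.2 compares age, sex, BMI and baseline VAS between groups and enters them in the primary analysis if a significant imbalance appears. Section 3.1.3 places the expectation score in sensitivity analyses for the primary outcome, again only if the groups differ significantly.
- **Missing data.** The mixed model is said to handle it under missing at random. Multiple imputation is planned as a sensitivity analysis.

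**The concern.** The two rules cover the same variables. Either could be reported as the result for function, gait or quality of life, and the choice could be made after the data are seen. Section 3.2.2 applies the 0.05 threshold to all analyses, so neither rule is marked as descriptive.

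Confounding matters more. Patients who choose the monitored, personalised programme may differ from those who choose conventional exercise in severity, motivation or expectation. The plan recognises this for the primary outcome and provides a remedy there. The Knee Pain Scale, Lysholm and SF-36 are open to the same self-selection and get no remedy. A difference in a secondary outcome could then reflect who chose which arm and not what the arm did.

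**Working it through.** **1. Do the two rules overlap?** The mixed-model rule is defined by visit schedule and the t-test rule by outcome class. The abstract puts outcomes in general on four visits, and section 3.1.2 removes no secondary outcome from that schedule. Each listed secondary outcome therefore meets both definitions. No sentence ranks the two analyses or names the visit for the secondary t-tests.

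**2. Does either rule adjust for confounding?**

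| Analysis of a secondary outcome | Terms stated | Confounders |
|---|---|---|
| Independent-samples t-test | group | none possible |
| Linear mixed model | group, time, group-by-time, subject | none listed |

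Moving from the t-test to the mixed model as written would settle the overlap but not the confounding.

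**3. How large could the confounding be?** The plan states no figure on this point. The inputs are:
- 43 per group, the planned evaluable number in section 2.6 (48 recruited less about 10% is 43.2). How section 2.6 derives 43 is a separate matter.
- Two-sided alpha 0.05 (section 3.2.2).
- Imbalance d, in SD, and its relation to the outcome. These are assumptions; the document gives none.

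With outcome SD 1, the standard error of the difference is √(2/43) = 0.2157. With no true effect and a bias b, the type I error is 1 − Φ(1.96 − b/0.2157) + Φ(−1.96 − b/0.2157).

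*One confounder*, correlation r with the outcome, b = d × r:

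| d | r | b | b/0.2157 | Type I error |
|---|---|---|---|---|
| 0.2 | 0.3 | 0.06 | 0.278 | 5.9% |
| 0.3 | 0.3 | 0.09 | 0.417 | 7.0% |
| 0.3 | 0.5 | 0.15 | 0.696 | 10.7% |
| 0.5 | 0.5 | 0.25 | 1.159 | 21.3% |

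*Four independent confounders*, each imbalanced by 0.3 SD with effect 0.3, so each shifts the difference by 0.09:
- All in one direction, total outcome SD 1: b = 4 × 0.09 = 0.36; 0.36/0.2157 = 1.669; type I error 38.6%. A simulation of 5,000 trials gave 39.3% unadjusted and 4.8% with all four adjusted.
- All in one direction, residual SD 1: total SD = √(1 + 4 × 0.09) = 1.166; b = 0.36/1.166 = 0.309; ratio 1.431; type I error 29.9%.
- Two each way: b = 0; type I error 5.0%.

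**4. How large could the missing-visit bias be?** The t-test uses only patients with a value at the visit. This was checked with 4,000 simulated trials per scenario, 48 per group, no true effect, and dropout after 6 weeks that depends on the 6-week value. Missingness and correlations are assumptions. Bias is in outcome SD.

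| Scenario | Missing | Complete-case bias | Likelihood-based bias | t-test type I error |
|---|---|---|---|---|
| Unequal correlations*, dropout in opposite directions by arm | 23.7% | 0.118 | −0.005 | 6.8% |
| Unequal correlations*, dropout tied to the 6-week value in control only | 21.7% | 0.066 | 0.003 | 5.6% |
| Correlation 0.6 throughout, opposite directions | 23.7% | −0.003 | −0.003 | 5.6% |

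*Baseline to 6 weeks 0.4, baseline to last visit 0.3, 6 weeks to last visit 0.7.

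The simulation standard error near 5% is √(0.05 × 0.95/4000) = 0.34 percentage points, so 5.6% is not clearly above nominal.

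**The case against.** **The two rules may be complementary.** The abstract pairs t-tests with between-group comparisons and mixed models with multiple time points. The t-tests could then compare change at one visit while the model describes the course over time. That reading is possible, but section 3.2.2 never says so for secondary outcomes, and the model's group-by-time term is itself a between-group comparison. The ambiguity stands. What falls is a count of tests: a reader might infer 27 or more t-tests (nine measures by three visits), but the document does not say that secondary outcomes are tested at each visit.

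**Adjustment may be meant more widely.** The abstract mentions adjusting for expectation without naming an outcome. Section 3.1.3 is more specific and ties it to the primary outcome, and a t-test could not carry it in any case.

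**Missing data are not ignored.** This is fair. Multiple imputation is planned directly after the t-test sentence. A reader might infer that incomplete patients are simply lost. In fact only the main t-test would be complete-case, with a sensitivity analysis behind it, and the bias in step 4 is modest or nil.

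**Covariance structure.** A reader might infer that random subject effects force the same correlation between visits 6 weeks apart and 3 years apart. The wording does not limit the model to a random intercept or exclude a structured residual covariance. That detail commonly belongs in an analysis plan, so no criticism is made of it.

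**Conclusion.** The point holds for the double assignment and for the absence of confounder adjustment in secondary outcomes. Both follow from the text and need no assumed figure.

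The size does rest on assumptions. With 43 per group, the unadjusted type I error could be about 5% if imbalances cancel, about 6% to 21% with one confounder (imbalance 0.2 to 0.5 SD, correlation 0.3 to 0.5), or about 30% to 39% with four 0.3 SD imbalances all acting in one direction. A reader might take the upper end as the expected error. The document does not support that, because it gives no imbalances, directions or prognostic strengths. Nor does adjustment guarantee 5%: it removes only the part due to measured confounders, and allocation by preference is likely to involve unmeasured ones.

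Missing-visit bias is a minor addition. It is probably small and depends on a missingness pattern that the document does not give.

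This should be corrected before the planned start in June 2026. It concerns the secondary outcomes; the primary 6-week t-test is a separate matter.

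**What to change.** In section 3.2.2, delete the secondary-outcome t-test sentence or label those tests descriptive. Name one linear mixed model as the main analysis of every repeated continuous secondary outcome, with:
- group, categorical time and group-by-time;
- a prespecified covariate set from data the plan already collects: baseline value of the outcome, age, sex, BMI, baseline VAS and treatment expectation score;
- covariates entered whatever the baseline significance tests show;
- the adjusted group contrast reported at each visit.

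The set must be named outright. Pointing to the primary analysis would not do, because section 3.2.2 has no fixed set there: covariates enter only after a significant imbalance. With the baseline value as a covariate, the response should be the three post-baseline visits. Keep multiple imputation as the sensitivity analysis, and state that residual confounding by unmeasured factors remains.

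Cost: rewording, with the same data and software. The downside is slightly more complex model output and a few degrees of freedom.

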## Patient and public involvement

Patients and/or the public were involved in the design, or conduct, or reporting, or dissemination plans of this research. Refer to the Methods section for further details.
